## Abstract

The movements of the affected upper limb in infantile hemiplegia are slower and clumsy. This leads to a decrease in the use of the affected hand. The visual effect obtained using the mirror box and the observation of actions in another individual can activate the same structural neuronal cells responsible for the execution of these actions. This research will study the affected upper limb functionality in hemiplegia infantile from 6 to 12 years old after the application of two intervention protocols: observation action therapy and mirror therapy combined with observation action therapy. Children with a diagnose of congenital infantile hemiplegia will be recruited to participate in a randomized controlled trial with two intervention protocols during four weeks (1 h per/day; 5 sessions per/week): Mirror Therapy Action Observation (MTAO) or Action Observation Therapy (AOT). The study variables will be: spontaneous use, measured with the Assisting Hand Assessment (AHA); manual ability measured with the Jebsen Taylor Hand Function Test (JTHFT); surface electromyography of the flexors and extensors muscles of the wrist and grasp strength through a grip dynamometer. Four assessments will be performed: At baseline situation, at the end of treatment, 3 and 6 months after treatment (follow-up assessments). This study will study the effects of these therapies on the use of the affected upper limb in children with hemiplegia.

## 1. Introduction

Infantile hemiplegia is a subtype of infantile cerebral palsy (CP), characterized by the involvement of one of the halves of the body due to a brain injury. Its prevalence is one case per 1300 live births [1]. The upper limbs are affected more than the lower limbs. The affected hand has a deficit in proprioception and tactile perception, which hinders fine motor skills, generally those of the fingers and the strength exerted by them [2]. Movements in the affected upper limb are slower and clumsy and are accompanied by mirror movements (MM) which are involuntary symmetrical movements observed in the contralateral upper limb to the voluntary upper limb movements. These movements are temporally observed in the development of the healthy child and then disappear. When these movements are subsequently present, they are considered abnormal [3]. Mild MM are common in preschool children but often appear in children with hemiplegia [4]. Although the mechanisms of mirror movements are not fully understood, it is likely that they are due to abnormal organization of the development of the motor system. Thus, alterations in the maturation of the transcallosal pathways have been suggested [4,5]. Moreover, children with hemiplegia have deficits in the selective control of the affected fingers and a diminished use of them. [6]. Consequently, the use of the affected hand is reduced, which is commonly known as “developmental neglect”, affecting activities of daily living [7,8,9].

Spasticity is defined as “a sensory-motor control disorder resulting from an injury to the upper motor neuron, which presents as an involuntary intermittent or sustained activation of the muscles” [10]. The spasticity includes the velocity-dependent increase in tonic stretching reflexes (muscle tone) and phase stretching reflexes (exaggerated tendon jerk) [11], as well as flexor and extensor spasms, flexor reflexes and altered motor control. Clinically, it is often difficult to differentiate the spasticity from the symptoms and signs caused by structural changes in the muscles [10,11].

Children with spastic hemiplegia show significant restriction in their daily activities due to the limited active range of movement of the affected upper limb, specifically in the elbow, as well as the alterations in muscle activity observed by electromyography. Thus, the affected side shows more co-contractions than the non-affected side. Surface electromyography is a good evaluation system to assess the activation of the motor unit in children with hemiplegia [12,13,14]. The restriction on the child’s participation in the environment due to the non-use of the affected upper limb is caused by the lack of exteroceptive and proprioceptive information at cortical level, as a consequence of the brain injury [15,16]. Therefore, the deficits in the structure, as well as the decrease in the movement amplitude or the spasticity would not be the exclusively causes of the activity limitation [16]. This developmental restriction decreases the learning to use the affected upper limb, producing exclusive dominance of the unaffected upper limb. The child uses compensatory strategies to avoid using the affected side [16]. This non-use increases muscle tone, reduces active movement, affects the growth of the affected upper limb and reduces the strength of this arm [16,17].

Increased muscle tone due to spasticity is often reduced using antispastic treatment (botulinum toxins, phenol…) [18]. However, these treatments do not necessarily improve upper limb functionality. An improvement in the quality of movement can appear, but it would not increase the spontaneous use of the affected upper limb. Therefore, it may be necessary to use treatments that promote the function and activity-participation to improve the functionality of the affected upper limb and its performance in daily life [19].

Mirror therapy is based on visual stimulation [20]. During mirror therapy, a mirror is placed on the midsagittal plane of the person, reflecting the unaffected side as if it were the affected side [20]. Therefore, the movements of the unaffected side create the illusion of normal movements of the affected side [21]. The illusion of the mirror can prevent or reverse a learned non-use of the affected limb [22]. One of the advantages of this therapy is its use as a self-administered home therapy [21]. Bruchez et al. [23] have shown the efficacy of mirror therapy in children with hemiplegia aged 6 to 18 years, improving the quality of movement and perception of the affected upper limb through feedback visualization of the healthy limb [23]. The replacement of the visual information of the affected upper limb with a mirror reflection of the non-affected upper limb improves motor control of children with unilateral cerebral palsy or hemiplegia [24] and obstetrical brachial palsy [24]. In hemiparesis, visual feedback increases the excitability of the ipsilateral motor cortex, optimizes the congruence between afferent (visual) feedback and promotes an internal representation of motor movements [25].

The positive effects could result from the coupling between the two upper limbs. This is supported by evidence that such simultaneous movements with both affected and unaffected limbs modulate interhemispheric inhibition, allowing the unaffected hemisphere to facilitate activation of the affected hemisphere. [26]. On the other hand, it has been shown that the observation of actions in another individual can activate the same neuronal structures, responsible for the execution of these actions, known as the mirror neuron network. From here appears the AOT, which stimulates the motor behaviour of the affected upper limb through the observation of sequences of systematic activities and their subsequent execution [27,28]. Transcranial magnetic stimulation (TMS), used while the subject was observing the actions, showed an increase in the excitability of the corticospinal tract, resulting in muscle contraction patterns very similar to those observed in action, favouring motor activity. Hence, as there is a greater corticospinal activation, there could be a greater cortical representation and therefore an increase in the spontaneous use of the affected upper limb in infantile hemiplegia [28].

No literature describing research combining mirror therapy and action observation could be found. Their combined use could increase the perception of the affected upper limb and facilitate motor recruitment and quality of movement, through visual illusion. In addition, with action observation, the spontaneous use and participation of the affected upper limb in daily activities through repetition of observed tasks can be increased. The combination of mirror therapy and the action observation therapy (MTAO) could facilitate the quality of movement of the upper limb, improving its structure and function and providing greater cortical activation and spontaneous use, through the repetition of specific movements. Furthermore, it can be done at home using a single intervention protocol. Conducting the therapy in the child’s home can involve the child in repeated practice of tasks and involve the family in the treatment process [29]. It has been reported that parents of children with disabilities have higher levels of stress than parents of typically developing children [30], which may suggest that the home is a viable setting for implementing therapy with parents. Their collaboration in producing target settings for treatment programs that involve family values and priorities may decrease the parents’ stress level [31]. The application of MTAO has a great clinical implication, since it is a low intensity program, which can be carried out at home with the follow up of a therapist, reducing economic costs and improving the interaction family—child—therapist.

The aim of the research will be to study the functionality of the affected upper limb in hemiplegia in children aged 6 to 12 years after applying two intervention protocols: MTAO and AOT”.

The hypotheses are: (1) “Both MTAO and AOT improve the functionality of the affected upper limb, with the effect of MTAO being greater” (2) “MTAO increases the spontaneous use and the manual ability in the affected upper limb more than AOT”. (3) “MTAO improves the muscle activity of the affected hand and increases grip strength more than AOT”.

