## 2. Materials and Methods

### 2.1. Study Design

A simple-blind (rater) randomized controlled pilot study will be carried out using two groups: AOT (control group) and MTAO (experimental group).

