### 2.3. Participants

The participants will be recruited in Spain. The recruitment will be from October 2019 to March 2021. To obtain the sample, a dissemination campaign has been carried out through social networks, the Spanish infantile hemiplegia association Hemiweb and different health professionals involved in the management of these patients, following these inclusion and exclusion criteria.

Inclusion criteria:Congenital infantile hemiplegia.Aged between 6 and 12 years.Lack of use of the affected upper limb.Level I–III of the Manual Ability Classification System (MACS). Level I: handles objects easily and successfully; level II: handles most objects but with reduced quality and/or speed of achievement and level III: handles objects with difficulty; needs help to prepare and/or modify activities [32].Level I–III in the Gross Motor Function Classification System (GMFCS). Level I: can walk indoors and outdoors and climb stairs without using hands for support, can perform usual activities such as running and jumping and has decreased speed, balance and coordination; level II: can climb stairs with a railing, has difficulty with uneven surfaces, inclined or in crowds of people and has only minimal ability to run or jump and level III: walks with assistive mobility devices indoors and outdoors on level surfaces, may be able to climb stairs using a railing and may propel a manual wheelchair and need assistance for long distances or uneven surfaces [33].

Exclusion criteria:Disease not associated with congenital hemiplegia.Low cognitive level compatible with attending a special education school.Presence of contractures in the affected upper limb affecting the functional movement.Surgery in the six months previously to the treatment.Botulinum toxin in the two months previously to or during the intervention.Pharmacologically uncontrolled epilepsy.

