In the execution, the child will have to watch the video and execute the observed action in the best possible way. The observed action will be repeated for 4 min. All the activities included in the protocol will be observed and imitated during a total time of 60 min without resting periods. During the sessions, each child should sit on a chair with both arms on a table in front of a monitor screen placed 1 m away. The parent will sit on the child’s affected side and should encourage the child by giving verbal suggestions without making any demonstration.

For the MTAO group, the first 15 min will be assigned to the mirror therapy and the remaining 45 min to the action observation therapy. In the first part of the mirror therapy, six activities to be performed with both upper limbs/hands symmetrically have been designed. Even if the affected upper limb cannot successfully complete the proposed action, the child will be asked to do it to the best of his or her ability. (Table 2).

The action observation therapy will be carried out for 45 min (after mirror therapy), using the same activities as in the AOT group (Table 2) and the same positioning of the child, but in this group 3 min are allocated for the visualization and execution of each set without resting during the execution.

Both protocols will include 60-min sessions. The MTAO protocol, begins with 15 min of mirror therapy, followed by 45 min of AOT with a duration of 3 min for each activity, in order to complete 60 min.

The randomization method will be carried out using the Epidat v. 4.2 software (Consellería de Sanidade, Xunta de Galicia, 15703, Spain), which, after a simple randomization process and consecutive sampling, will divide the participants into two groups (TOT and MTAO) with a number of 10 participants per group. A numerical sequence will be obtained which will be kept in opaque sealed envelopes. The envelopes will be opened by a blind researcher, who will decide at random, according to the randomization sequence. Although subject recruitment has begun, due to the Coronavirus pandemic, the trial has been delayed until the follow-up of participants can be ensured.

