### 2.5. Outcome Measures

Four assessments will be performed. The first assessment will be focused on obtaining the data before the treatment and sociodemographic variables (including age and sex), i.e., in week 0 (baseline situation, immediately before starting treatment), whereas the second assessment will be conducted at the end of the treatment, i.e., in week 4 (a total dose of 20 h). Moreover, two follow-up assessments will be done: 3 month and 6 months after treatment in both protocols (Figure 1).

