### 2.6. Data Analysis

Statistical analyses will be performed with SPSS v.24.0 (SPSS Inc., IBM, Chicago, IL, USA). Statistical significance will be set at *p* < 0.05. The test Shapiro-Wilk test will be used to study normality of the sample.

A descriptive analysis of demographic variables will be performed using means and standard deviation for normal distribution variables, and medians and interquartile ranges for non normal distribution variables. The categorial variables will be described using frequencies and %.

To evaluate statistically significant differences intergroup in the variables at baseline, the independent Samples T-test (normal distribution) or the Mann-Whitney U test (non normal distribution) will be used. To study the effects of the interventions on the outcomes measures at four time points, for normal distribution variables, a two-way (intervention × time) repeated measures ANOVA test will be conducted. The Bonferroni correction will be employed for pairwise post-hoc comparisons to further analyze significant interactions. The Greenhouse–Geisser adjustment will be applied to correct for the lack of sphericity (Mauchly’s sphericity test, *p* < 0.05) whenever is necessary. For non-normal distribution variables, the Friedman test will be used. Bivariate correlation coefficients will be estimated to examine the relationship between the subjects’ age, sex, or affected upper limb.

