This research has some limitations. Firstly, the lack of cross-cultural validation in Spanish of some of the measurement tools used, such as the AHA. In addition, a group with conventional intervention has not been included. As strengths, it highlights that it is the first research to evaluate the effect of mirror therapy combined with action observation therapy on upper limb functionality. In addition, the intervention protocols will be carried out at home, which means reducing economic costs and optimizing family resources. Finally, the results will improve clinical practice.

The results of our randomized controlled trial will be disseminated to the scientific community through scientific (peer-reviewed) journals and congress. In addition, research results will be presented to stakeholders, including patients, families and physicians.

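### The clause of hypothesis 1 that both therapies improve function cannot be tested as a treatment effect, because nothing in the design separates therapy from change over time

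*Protocol article*

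**What the plan says.** The last paragraph of the Introduction gives three hypotheses. The first reads: "Both MTAO and AOT improve the functionality of the affected upper limb, with the effect of MTAO being greater". It joins an absolute claim for each arm to a comparative claim. Hypotheses 2 and 3 are comparative (MTAO more than AOT).

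Section 2.1 sets up a randomised pilot study "using two groups: AOT (control group) and MTAO (experimental group"). Section 2.4 shows how much the arms share: in the MTAO group "the first 15 min will be assigned to the mirror therapy and the remaining 45 min to the action observation therapy", using the same activities as the AOT group.

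Section 2.5 places the only pre-treatment assessment "in week 0 (baseline situation, immediately before starting treatment"). The others are at the end of the four-week treatment and at follow-up: "two follow-up assessments will be done: 3 month and 6 months after treatment in both protocols". Section 2.3 admits children "Aged between 6 and 12 years".

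In section 2.6, for normally distributed outcomes, "a two-way (intervention × time) repeated measures ANOVA test will be conducted", with post-hoc comparisons to follow up significant interactions. For non-normal outcomes the article names the Friedman test. The Discussion lists as a limitation that "a group with conventional intervention has not been included", but does not connect this to hypothesis 1.

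**The concern.** A claim that a therapy improves function needs a comparison with its absence. This design offers none: no untreated, usual-care or waiting-list arm, and no repeated pre-treatment measurement from which a trend without therapy could be judged. Comparing MTAO with AOT does not help with this clause. Both arms do the AOT activities, so any effect of AOT is largely common to them and is not identified by their difference.

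Only the within-arm change, the time term of the ANOVA or the Friedman test can speak to the clause. Each answers whether scores changed, not why. Shared change is plausible: the children are developing, and they repeat the same tests four times.

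What is at stake is the conclusion the trial may report. It is sized for a very large between-arm effect (1.40). If the true difference is smaller, the contrast may well be non-significant, and a finding that both therapies improved function would then be at hand, because the hypothesis was written that way.

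**Working it through.** **1. What the planned size was built for.** Inputs from section 2.2: effect size 1.40, 80% power, 10 per group. Sections 2.2 and 2.6 print the significance level differently (0.05% and p < 0.05); I use two-sided 0.05.

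Two-sample t test with n per group: df = 2n − 2, non-centrality = 1.40 × √(n/2).
- n = 10: df = 18, non-centrality = 1.40 × √5 = 3.13, critical t = 2.10, power 0.841.
- n = 9: power 0.796.

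The smallest n reaching 80% is 10, the stated figure. The sample size therefore fits a comparison between arms, not within-arm change.

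**2. What supports each clause of hypothesis 1.**

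| Clause | Evidence available | Protected by randomisation? |
|---|---|---|
| Both therapies improve function | Within-arm change, ANOVA time term, Friedman test | No |
| MTAO has the greater effect | Intervention × time interaction | Yes |

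**3. How often time alone gives a significant result (illustration).** The article gives no drift, SD or between-visit correlation, so these are assumed. Set-up: 2 arms × 4 visits, 10 per arm, outcome SD 1, equal correlation ρ between visits, no effect of either therapy, the same shift in both arms, mixed ANOVA at 0.05, 4,000 runs.

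| Shared shift | ρ = 0.7 | ρ = 0.8 | ρ = 0.9 |
|---|---|---|---|
| 0.2 SD, complete by week 4 | 18% | 26% | 49% |
| 0.3 SD, complete by week 4 | 37% | 54% | 86% |
| 0.3 SD, linear over months 0, 1, 4, 7 | 31% | 45% | 77% |

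Entries are the share of trials with a significant time effect. With no shift it is about 5%. The interaction is significant in about 5% throughout. Repeat runs differ by a point or two.

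**4. Both terms together.** With the 0.3 SD step, time and interaction are both significant in only 2.3%, 3.0% and 4.7% of runs, before requiring that MTAO be the better arm.

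**5. Check without simulation.** A paired t test on n children with a shift of k SDs of the change score has non-centrality k√n. For k = 0.5:
- One arm, n = 10: 0.5 × √10 = 1.58, critical t = 2.26, probability of a significant rise 0.29.
- Both arms separately significant: 0.293² = 0.09.
- All 20 children pooled: 0.5 × √20 = 2.24, critical t = 2.09, probability 0.56.

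To link this to step 3, the change score has SD √(2(1 − ρ)). At ρ = 0.8 that is √0.4 = 0.63, so a 0.3 SD shift is 0.3/0.63 = 0.47 SDs of change. The pooled 0.56 at k = 0.5 is in line with the simulated 54%.

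**The case against.** The strongest reply is that the trial is already mostly comparative. Hypotheses 2 and 3 compare the arms, the Discussion states the aim as a comparison, the sample size is a two-sample calculation, and post-hoc tests are tied to significant interactions. Nowhere does section 2.6 say that the time term will be read as efficacy. The missing group is disclosed and the study is called a pilot. All of this stands and limits the point to one clause. It does not remove it: the clause is still a stated hypothesis, the limitation does not narrow it, and no analysis plan can supply the missing comparison.

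Several stronger readings are tempting but not supported:

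- **That all of hypothesis 1 could be confirmed from change over time.** It is a conjunction, and its second half needs the randomised interaction. The 37% to 86% is an error rate for the first clause, not for the hypothesis; step 4 shows how rarely both terms reach significance.
- **That these rates measure this trial.** They depend on an assumed drift, and a step completed by week 4 is unfavourable for growth, which accrues gradually.
- **That regression to the mean and concurrent care are established biases.** Entry requires lack of use of the limb but sets no cut-off on a measured outcome, and concurrent care is not described. Both are possible only.
- **That the timed nature of the hand test drives the problem.** This applies to the JTHFT. The main outcome, the AHA, is a videotaped play session scored by a blinded rater.
- **That the Conclusions overclaim.** Section 4 speaks of functional changes after the therapies and is neutral.

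**Conclusion.** The point holds for the first clause of hypothesis 1 only. With two active arms that share the AOT activities, one pre-treatment assessment and no untreated or usual-care comparison, a significant change over time cannot be attributed to either therapy. This follows from the design and needs no numerical assumption.

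The size does rest on assumptions. With no treatment effect, 10 per arm and a shared 0.3 SD step, the time effect is significant in roughly 37% to 86% of trials for correlations of 0.7 to 0.9. The range is 31% to 77% if the same drift accrues linearly, and 18% to 49% for a 0.2 SD step.

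The claim that MTAO is better than AOT, and hypotheses 2 and 3, rest on the randomised contrast and are unaffected by this point. The Friedman test for non-normal outcomes contains no between-arm term, but that is a separate matter.

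**What to change.** - Restate hypothesis 1 as the between-arm contrast: MTAO improves AHA more than AOT. Hypothesis 2 already compares the arms on spontaneous use, which the AHA measures, so the two should be worded without duplication.
- Report change from baseline within each arm descriptively, with 95% confidence intervals, and state that it is not evidence that either therapy works. Within-arm p-values need not be forbidden if they are labelled descriptive.
- In the Discussion, link the limitation about the missing conventional group to this restriction: the trial can say whether MTAO differs from AOT, not whether either is better than neither.

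No new arm, visit or participant is needed. The cost is the wording of one hypothesis, one reporting rule and one limitation. The trial gives up a within-arm efficacy claim that it cannot support; keeping it as a causal claim would require an untreated, usual-care or waiting-list comparison.
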